# A multicenter double-blind randomized crossover study comparing the impact of dorsal subthalamic nucleus deep brain stimulation versus standard care on apathy in Parkinson’s disease: a study protocol

**DOI:** 10.1186/s13063-024-07938-9

**Published:** 2024-02-03

**Keywords:** Neurology, Parkinson’s disease, Apathy, Deep brain stimulation, Randomized controlled trial

## Abstract

**Background:**

Neuroimaging studies suggest an association between apathy after deep brain stimulation (DBS) and stimulation of the ventral part of the subthalamic nucleus (STN) due to the associative fibers connected to the non-motor limbic circuits that are involved in emotion regulation and motivation. We have previously described three patients with severe apathy that could be fully treated after switching stimulation from a ventral electrode contact point to a more dorsal contact point.

**Objectives:**

To determine whether more dorsal stimulation of the STN decreases apathy compared to standard care in a multicenter randomized controlled trial with a crossover design.

**Methods:**

We will include 26 patients with a Starkstein Apathy Scale (SAS) score of 14 or more after subthalamic nucleus (STN) deep brain stimulation (DBS) for refractory Parkinson’s disease. This is a multicenter trial conducted in two teaching hospitals and one university medical center in the Netherlands after at least 3 months of STN DBS. Our intervention will consist of 1 month of unilateral dorsal STN stimulation compared to treatment as usual. The primary outcome is a change in SAS score following 1 month of DBS on the original contact compared to the SAS score following 1 month of DBS on the more dorsal contact. Secondary outcomes are symptom changes on the Movement Disorders Society-Unified Parkinson’s Disease Rating Scale motor part III, Montgomery-Åsberg Depression Rating Scale, 39-item Parkinson’s disease questionnaire, Parkinson’s disease impulsive-compulsive disorders questionnaire, changes in levodopa-equivalent daily dosage, apathy rated by the caregiver, and burden and quality of life of the caregiver.

**Trial registration:**

ClinicalTrials.gov NL8279. Registered on January 10, 2020.

**Supplementary Information:**

The online version contains supplementary material available at 10.1186/s13063-024-07938-9.

### Objectives {7}

We will test whether STN DBS-related apathy could be treated by switching stimulation from a ventral to a more dorsal contact point on the electrode. Additionally, we aim to investigate whether these adjusted stimulation parameters have effects on PD motor manifestations, psychiatric symptoms, and quality of life of the participant and their caregivers. 

### Trial design {8}

This is a multicenter prospective randomized open-label blinded endpoint crossover superiority trial.

## Methods: participants, interventions, and outcomes

### Study setting {9}

In this study, we will determine whether more dorsal stimulation of the STN decreases apathy compared to treatment as usual, including 26 PD patients suffering from apathy after ≥ 3 months of STN DBS. The Consolidated Standards of Reporting Trials (CONSORT) study schedule is shown in Fig. 1. The participating centers are Amsterdam University Medical Centers (Amsterdam UMC), St. Elisabeth TweeSteden ziekenhuis (ETZ), and HagaZiekenhuis (HZ). The first participant was included in February 2020. The study protocol was approved by the Medical Ethics Committee of the Amsterdam UMC, and the study is registered at the Netherlands Trial Register (number NL8279), currently included in the International Clinical Trial Registry Platform.

**Fig. 1 Fig1:**
[figure not shown]
Inclusion and randomization

### Eligibility criteria {10}

The inclusion criteria are as follows: (a) idiopathic PD, (b) at least 3 months of STN DBS treatment, and (c) a score of 14 or more points on the Starkstein Apathy Scale (SAS). Exclusion criteria are as follows: (a) perioperative intracerebral complications related to STN DBS surgery (e.g., bleeding or infection) inflicting permanent changes, (b) cognitive decline, as measured by a Montreal Cognitive Assessment (MoCA) score of 25 or less, (c) participants who are not sufficient in the Dutch language, (d) participants who are already stimulated on the most dorsal contact point on both electrodes, and (e) no written informed consent.

### Who will take informed consent {26a}

Participants will be included and randomized after they sign the informed consent form obtained by a nurse practitioner or clinician. A nonprofessional caregiver, if one is available for the participant, will be asked to fill in informant-rated questionnaires at every timepoint.

### Additional consent provisions for collection and use of participant data and biological specimens {26b}

This trial does not involve collecting biological specimens for storage.

## Interventions

### Explanation for the choice of comparators {6b}

In an earlier case study, we presented three patients with severe apathy that were treated by switching stimulation from a ventral electrode contact point to a more dorsal contact point [18]. This increase in apathy after DBS was possibly related to collateral stimulation of limbic fibers [16, 17].

### Intervention description {11a}

Every DBS patient programmer will be installed with three programs; one is the escape option and will contain the original stimulation settings, and the other two contain either the investigational or the control settings. The investigational program stimulates one stimulation point more dorsally on the side with the most ventral active contact point relative to the AC-PC line based on the fused preoperative MRI and postoperative CT-scan images. The total duration of the visits of each included subject is 20–30 min per visit, for a total of three visits in 2 months (Table 1).

**Table 1 Tab1:** Assessment schedule

	Pre-operative	Post-operative	Inclusion	Baseline	Visit 1 (+ 1 month)	Visit 2 (+ 2 months)	End of trial
SAS	X		X	X	X	X	
MRI, DTI	X						
CT scan		X					
In- and exclusion criteria			X				
MOCA			X				
Baseline characteristics				X			
MDS-UPDRS-III	X			X	X	X	
PDQ-39				X	X	X	
QUIP	X			X	X	X	
LEDD	X			X	X	X	
MADRS	X			X	X	X	
AES-I*				X	X	X	
SF-36*				X	X	X	
Suspected arm							X
Preferred settings							X

*SAS* Starkstein’s Apathy Scale, *MOCA* Montreal Cognitive Assessment, *MDS-UPDRS-III* Movement Disorder Society’s Unified Parkinson’s Disease Rating Scale, motor part III, *MADRS* Montgomery-Åsberg Depression Rating Scale (MADRS), *PDQ-39* 39-item Parkinson’s disease questionnaire, *QUIP* Parkinson's Disease Impulsive-Compulsive Disorders Questionnaire, *LEDD* levodopa-equivalent daily dosage, *AES-I* Apathy Evaluation Scale, a second apathy scale rated by the informal caregiver if the patient has one. *SF-36* Short-Form Health Survey. Suspected arm, patients will be asked to choose which arm they think they were randomized for. Preferred settings, patients will be asked to choose which of the settings they will continue with. *Although the timing for these questionnaires is the same as the visits for the patients, these questionnaires might be sent by regular mail to the informed caregiver

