### Outcomes {12}

The primary outcome is the comparison of the Starkstein Apathy Score (SAS) score following 1 month of DBS on the original contact and the SAS score following 1 month of DBS on the more dorsal contact [19]. Secondary outcomes are symptom changes on the Movement Disorders Society-Unified Parkinson’s Disease Rating Scale motor part III (MDS-UPDRS-III) [20]. Montgomery-Åsberg Depression Rating Scale (MADRS) [21]. 39-item Parkinson’s disease questionnaire (PDQ-39) [22]. Parkinson’s Disease Impulsive-Compulsive Disorders Questionnaire (QUIP) [23]. changes in levodopa-equivalent daily dosage (LEDD) [24]. apathy rated by the caregiver (AES-I) [25]. and burden and quality of life of the caregiver (SF-36) [26]. Additionally, participants will be asked which program they thought contained the investigational settings (i.e., “first,” “second,” or “unsure”) and which program they wish to continue to use (i.e., first or second). The preoperative MRI, postoperative CT-scan, and preoperative SAS scores will be retrospectively collected to provide supplementary information about the relationship between apathy and stimulation location.

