### Methods for additional analyses {20b}

The SAS follow-up scores will be further investigated using McNemar tests, paired *t*-tests, and Wilcoxon signed-rank tests taking into account patients’ MDS-UPDRS-III, SAS, MADRS, QUIP, LEDD, PDQ-39, AES-I, and SF-36.

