## Discussion

Patients suffering from PD often experience neuropsychiatric symptoms, which might even be the first detectable symptom of this neurodegenerative process [37]. DBS has great potential to relieve motor symptoms and may also have a beneficial effect on many non-motor symptoms [3, 27, 38]. One of the main challenges in the management of advanced PD and STN DBS is increased apathy after STN DBS with a high impact on quality of life [7]. The pathophysiology of apathy in PD, and particularly in the case of STN DBS, is still not fully understood; however, the relation between apathy and medication reduction and a direct stimulation effect are recognized as potential factors [9]. Because our proposed intervention is only a minor adjustment in the stimulation settings, this adjustment has the potential to improve the quality of life of many PD patients relying on STN DBS without many side effects. The application of STN DBS may subsequently be expanded as a patient’s mood might benefit from the treatment of invalidating PD motor and hypodopaminergic non-motor symptoms, as well as the possible reduction of hyperdopaminergic side effects that are allowed by lowered LEDD following STN DBS. The reduction of apathy might further increase physical health of people with PD who might have been limited in their activities by apathy and improve their social life. The study design has some limitations: first, the contact point that will be selected for the intervention will not be based on MRI imaging. This practice has been chosen because of the concept generalization; in this way, our intervention could be applied regardless of access to visualization of the STN subregions which are difficult to distinguish. The imaging of these subregions would preferably be done requiring imaging instruments on the level of 7-Tesla MRI scans, which is almost exclusively used for research and not clinical practice. Another argument for our decision was the desire to not influence the selection of intervention based on our hypothesis but to apply the intervention that has worked for previous patients [18]. However, this contact point was not necessarily closest to the motor region of the STN. Benefits of choosing the contact closest to the motor region of the STN on MRI imaging might have been the following: a more optimal motor response with possibly less required adjustments in LEDD or DBS current and less risk of stimulating adjacent regions with possible additional side effects. Second, we chose an apathy score of 14 or more on the SAS as inclusion criteria instead of an increased SAS score between pre- and postoperative assessments, which would more likely indicate solely STN DBS-induced apathy. Our argument for this decision was also generalizability because STN DBS-treated patients with apathy will have rarely available preoperative apathy scores for comparison. Furthermore, other studies found that STN DBS improved apathy or PD-related dysphoria without an earlier increase of apathy following STN DBS [39, 40]. Third, this study focused on apathy, although apathy is associated with other disorders. For example, apathy and depression share many features and might have some common pathophysiology when related to PD. We chose to include the most common disorders as secondary outcomes and not exclude participants with a current depressive or psychotic episode [3, 9, 41, 42]. Fourth, enrollment of participants was possible after only 3 months of STN DBS which might arguably be too soon because many centers optimize DBS stimulation and dopaminergic medication in the first 6 months. We chose the timepoint of at least 3 months because of four reasons: optimization of DBS and medication within 3 months are prioritized in our center, an earlier study showed that apathy did not further increase after 3 months [43]. cognitive decline might develop in the timespan of DBS surgery and optimization, and waiting on drugs for the treatment of depressive episodes to have effect was deemed inconsequential because this study aimed to treat apathy regardless of depressive symptoms. Fifth, 1 month of intervention is relatively short, we opted for this period because in our case study, and the direct stimulation effect was resolved within days to weeks [18]. This fast effect was also present in another case study [7]. To our knowledge, these are the only intervention reports on an imaging-supported STN DBS stimulation effect on apathy. However, relative to most non-motor symptoms and psychiatric disorders, an intervention of 1 month is short, and this could restrict the effectiveness of the trial. We hypothesize that switching stimulation to the motor region of the STN could be an optimization for DBS in PD, with an effect on multiple psychiatric symptoms and quality of life.

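### The contact is moved on one lead only, but the motor outcome has no score tied to that lead, so a one-sided motor change would be estimated imprecisely

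*Protocol article*

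**What the plan says.** The Abstract (Methods) describes a one-sided intervention: "Our intervention will consist of 1 month of unilateral dorsal STN stimulation compared to treatment as usual". Intervention description {11a} says how the side is chosen: the programme "stimulates one stimulation point more dorsally on the side with the most ventral active contact point". The moved lead may therefore be the left in one patient and the right in another.

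Objectives {7} include asking "whether these adjusted stimulation parameters have effects on PD motor manifestations, psychiatric symptoms, and quality of life". Outcomes {12} meets the motor part of that aim by listing change on the "Rating Scale motor part III (MDS-UPDRS-III") among the secondary outcomes, and Table 1 schedules the scale at baseline, Visit 1 and Visit 2. Methods for additional analyses {20b} names paired tests "taking into account patients’ MDS-UPDRS-III, SAS, MADRS, QUIP, LEDD, PDQ-39, AES-I, and SF-36". None of these sections mentions a score for one side of the body, and none sets a motor margin.

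The Discussion recognises a possible motor price. Of the chosen contact it says: "However, this contact point was not necessarily closest to the motor region of the STN". It also says that the adjustment has the potential to "improve the quality of life of many PD patients relying on STN DBS without many side effects".

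**The concern.** Each subthalamic lead is expected to act mainly on the opposite side of the body. If one lead is shifted and the other left alone, a motor change should show chiefly in the limb items opposite the shifted lead. The full MDS-UPDRS-III adds the limbs served by the unchanged lead and the axial items. If those items do not respond to the shift, they add variance to the paired difference and no signal.

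What is at stake is the precision of the motor answer. The trial expects about 21 patients with complete data, and its size was set for apathy, not for motor change. A wide interval around the total-score difference would leave open whether the shift costs motor function on the side it acts on. Because the side varies between patients, a fixed left or right subscore would not help. The score has to be defined by the moved lead, and that is best written down before the data are analysed.

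**Working it through.** **The plan's own figure.** The only power calculation in the article is for the SAS (Sample size {14}): difference 8, SD of paired differences 12, two-sided 5%. With the noncentral t and n − 2 degrees of freedom, power is 0.805 at n = 20 and 0.826 at n = 21, so the stated 80% reproduces. With 26 recruited and 20% dropout, 26 × 0.8 = 20.8, or about 21 complete patients. No such calculation is given for MDS-UPDRS-III.

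**Inputs for the illustration.** From the article: n = 21, two-sided 5%, a within-patient contrast. Assumed, because the article gives no motor figures: a true loss of 3 points on the opposite-side limb items; SD of the paired difference 5 for that subscore (s_c) and 7.5 for all remaining items (s_r); correlation r = 0.3 between the two; no change in the remaining items.

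**Size in points.** The total is a sum, so its mean change is 3 + 0 = 3. The loss is not shrunk.

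**Noise.**
- Var(total) = s_c² + s_r² + 2·r·s_c·s_r = 25 + 56.25 + 22.5 = 103.75
- SD(total) = √103.75 = 10.2
- Variance ratio = 103.75 / 25 = 4.15

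**Power (noncentral t, df = 20).**
- Side score: 3/5 = 0.60 SD, power 74%
- Total: 3/10.2 = 0.29 SD, power 25%

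**Half-width of the 95% CI, t × SD/√21 with t = 2.086.**
- Side score: 2.086 × 5/4.583 = 2.3 points
- Total: 2.086 × 10.19/4.583 = 4.6 points

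**Varying SDs and correlation.** With s_c from 4 to 6, s_r/s_c from 1.25 to 2 and r from 0 to 0.6, power is 59–90% on the side score and 13–53% on the total, with a variance ratio of 2.6 to 7.4. A second set of assumptions gives the same direction: equal SD on both body sides, midline SD 0 to 1 times a side's SD, and correlations 0 to 0.8. A loss that the side score detects with 80% power at n = 21 (0.645 SD) is then detected by the total with about 17–51% power.

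**Varying the no-signal assumption.** Both ranges above keep the other items unchanged. Returning to the central case and letting the remaining items worsen too:

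| Worsening in remaining items | Change in total | Power on total | Power on side score |
|---|---|---|---|
| 0 | 3 | 25% | 74% |
| 1 | 4 | 40% | 74% |
| 2 | 5 | 57% | 74% |
| 3 | 6 | 73% | 74% |

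The advantage of the side score therefore depends on the effect being largely one-sided. If the other items worsen as much as the side score, it all but disappears.

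**The case against.** The article names a scale. It does not say that only the total will be analysed or that item scores will be discarded. A side-specific subscore could stand in the full protocol or SAP, neither of which is shown, so its absence from the article is not in itself an error. That stands, and the point is put as an improvement to a stated secondary outcome.

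The total is also a legitimate target. The aim in {7} concerns motor manifestations in general, and a patient choosing between settings cares about overall motor state, axial function included. That is a good reason to keep the total. It is no reason to leave out a score that looks where the intervention acts.

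Motor harm has other routes: adverse event reports {22}, the escape programme {11a}, PDQ-39, and the participant's choice of programme {12}. These are useful, but none of them estimates motor change on the affected side, and programme choice mixes motor effects with effects on apathy.

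Two stronger readings are tempting. A reader might infer that the total shrinks a one-sided loss. It does not: the points survive unless other items improve, and only precision is lost. A reader might also infer that a non-significant motor result is set to be reported as absence of side effects. The article contains no such rule. The Discussion speaks only of a potential for benefit without many side effects, and it openly concedes that the contact may not be the best one for motor response.

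**Conclusion.** The point holds as a modest one. A one-lead intervention is paired with a motor outcome that has no component keyed to that lead, and in about 21 patients the total may give an imprecise answer to a question the article itself raises. In the central illustration, power is 25% on the total against 74% on the side score, and the 95% CI is about twice as wide (±4.6 against ±2.3 points).

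These figures rest on an assumed effect, assumed SDs and an assumed correlation, and on the remaining items carrying no signal. Nothing in the documents fixes any of these, so the figures show direction and plausible scale rather than a measured shortfall. The point concerns one secondary outcome and leaves the primary SAS comparison and the sample size untouched.

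**What to change.** In Outcomes {12} and Methods for additional analyses {20b}, keep the MDS-UPDRS-III total and add the limb-item subscore for the body side opposite the shifted lead. Analyse both with the same within-patient contrast (dorsal minus original contact), and report each difference with its 95% CI. State that a non-significant difference will not be read as absence of motor cost.

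The shifted side is known from programming and can be merged at analysis, so the assessor stays blinded. The same-side subscore may be shown descriptively. It is not a strict negative control, since an effect of the shift on that side cannot be ruled out.

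The cost is a sentence in each section and one more secondary estimate to report. The scale is already rated at baseline and both visits, so no visits or assessments are added, provided item scores are kept. The Trial status section reports recruitment as ongoing, with 16 of 26 participants finished, so the definition can still be fixed before analysis.

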### Criteria for discontinuing or modifying allocated interventions {11b}

Participants are allowed to change the stimulation by plus or minus 0.5 V or milliampere.

### Strategies to improve adherence to interventions {11c}

To improve adherence to intervention protocol, the blinded assessor will check whether the programs were switched by the participant during the trial.

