### Concealment mechanism {16b}

The blinded assessor is a second nurse practitioner, who will perform the 1- and 2-month follow-up assessment. The blinded assessor will not be able to access the stimulation settings of the programmer but will be able to switch from the first to the second program after 1 month.

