## Assignment of interventions: blinding

### Who will be blinded {17a}

Both the participant and the assessor will be blinded in this trial.

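### The formal design statement says open-label although participant and assessor are blinded, and the blinded assessor's programme-switch check permits a guess at allocation when the escape programme was used

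*Protocol article*

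**What the plan says.** On who is masked, the protocol article makes three statements:

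- Title: "A multicenter double-blind randomized crossover study".
- Trial design {8}: "This is a multicenter prospective randomized open-label blinded endpoint crossover superiority trial".
- Who will be blinded {17a}: "Both the participant and the assessor will be blinded in this trial".

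On the programmer, Intervention description {11a} says that three programmes are installed: "one is the escape option and will contain the original stimulation settings, and the other two contain either the investigational or the control settings". Outcomes {12} defines the control condition as stimulation on the original contact.

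On the assessor, Concealment mechanism {16b} describes a second nurse practitioner who performs both follow-up assessments and moves the participant from the first to the second programme after 1 month. It adds a safeguard: "The blinded assessor will not be able to access the stimulation settings of the programmer". Participant timeline {13} gives this blinded assessor the primary and secondary outcomes. Strategies to improve adherence {11c} then adds a further task: "the blinded assessor will check whether the programs were switched by the participant during the trial". The article does not say whether this check comes before or after the ratings, or at which visit it is made.

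**The concern.** The outcomes include apathy, mood and quality of life, all open to expectation. Whether participants knew their settings is therefore among the first things a reader of the primary result needs to know. An open-label label in the formal design statement tells that reader that participant expectation was uncontrolled, while the title and {17a} say the opposite.

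The adherence check raises a second issue. The person whose ignorance of allocation protects the ratings is asked to find out what the participant did with the programmer. One of the three programmes is not coded: its content is known to be the original settings. Learning that it was used tells the assessor something about the programme that was left, and each participant's two periods are complementary. What is at stake is assessor blinding for the participants who used the escape programme.

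**Working it through.** No figure in the plan bears on this point, so the check sets the statements side by side and follows what the assessor can learn.

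**Step 1: the label.**

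| Place in the protocol article | Fits a masked participant? |
|---|---|
| Title (double-blind) | Yes |
| Trial design {8} (open-label, blinded endpoint) | No |
| Outcomes {12}: participant is asked which programme was investigational, with unsure as an option | Yes; the question has little purpose if the participant knows |
| Who will be blinded {17a}: participant and assessor | Yes |
| Procedure for unblinding {17b}: codes held for breaking the blind | Yes |

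Only {8} stands apart.

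**Step 2: what the check can disclose.** The assessor does not see settings ({16b}), so the two study programmes are known only as first and second.

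| What the check shows | What the assessor learns |
|---|---|
| No switch | The settings stay undisclosed |
| Switch between first and second | Nothing about which is dorsal |
| Switch to escape | The stimulation in use is the original setting; the programme left may be guessed to be the dorsal one |

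**Step 3: how strong the guess is.** Randomisation is 1:1 ({16a}), so before the check the dorsal setting has probability 1/2 in a given period. Let p_d be the probability of escape use in a dorsal period and p_c that in a control period. Then

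P(dorsal | escape used) = (½·p_d) / (½·p_d + ½·p_c) = p_d / (p_d + p_c).

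- If p_d = p_c, this is 1/2 and the check carries no information.
- If p_d > p_c, it exceeds 1/2. This direction is plausible, because escape returns the participant to the contact already used in the control period.
- It equals 1 only if p_c = 0, and the article does not support that.

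The article gives neither p_d nor p_c. Escape use therefore permits an inference and does not establish the allocation. For rating bias, though, what matters is the assessor's belief, and the assessor can make the same argument.

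**Step 4: carry-over of knowledge between visits.** Each participant receives both conditions, so a guess at one period is a guess at the other. Assume the same individual rates both visits, as {16b} suggests.

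| When the assessor makes the check | Visit 1 ratings | Visit 2 ratings |
|---|---|---|
| At visit 1, before rating | Exposed | Exposed |
| At visit 1, after that visit's ratings are locked | Protected | Exposed |
| Only after visit 2 ratings are locked | Protected | Protected |

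Exposed here means only for a participant in whom the check has shown escape use.

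**The case against.** The strongest reply has four parts.

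- **The label is only wording.** Sections {16b} and {17a} state plainly who is masked, so {8} does not change how the trial runs. This stands as to conduct. It does not rescue {8}, which is the formal design statement and is wrong as written. It may have been meant to describe the staff who install the settings, but that is not what open-label conveys.
- **The settings are withheld from the assessor.** This is a real safeguard, and it removes most of the risk. A reader might infer that any recorded switch reveals both periods. The documents do not support that: a move between the coded programmes discloses nothing, and a masked participant may also leave the control programme. The safeguard does not cover escape use, where no settings need to be read.
- **The order of check and rating is not stated.** This is correct, and a condensed article may leave it to the full protocol. A reader might infer that the assessor learns of switching before rating; the article does not say so. Step 4 shows, however, that the order within visit 1 does not decide the matter for visit 2.
- **The article does not say whether the Starkstein Apathy Scale is rated by the assessor or completed by the participant.** It lists the scale among questionnaires. If the participant completes it, the assessor's knowledge matters much less for the primary outcome. This stands and limits what can be claimed.

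**Conclusion.** The contradiction in the design label is certain and needs correcting: {8} conflicts with the title and {17a}, and {12} and {17b} also fit a masked participant.

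The adherence check is a conditional weakness in assessor blinding. It arises only if the check shows that the escape programme was used, it permits a guess and not knowledge of the allocation, and the guess extends to the other period. It rests on three assumptions: the check shows which programme was in use, the same assessor rates both visits, and escape is likelier from the dorsal setting than from control.

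No magnitude can be given. A reader might want to state a share of paired differences affected, but the article gives no rate of escape use. Any percentage would be an assumed count divided by the sample size, and would say nothing about the bias in a rating. The point merits correction because the remedy is cheap, not because harm has been shown.

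**What to change.** 1. **Trial design {8}:** replace the open-label, blinded-endpoint description with double-blind (participant and assessor), to agree with the title and {17a}. This is a wording change only.
2. **Strategies to improve adherence {11c}:** assign the programme-use check to the unblinded nurse practitioner who already installs the settings ({13}), and state that the result is not passed to the assessor. Alternatively, let the assessor make the check only after all visit 2 ratings are entered and locked. Locking only the ratings of the same visit would still leave visit 2 open to what was learned at visit 1.

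The first option in item 2 costs a little coordination, because the installing nurse practitioner is described only at set-up and would have a task at follow-up. The second costs later feedback on adherence. Trial status reports 16 of 26 participants finished by 15 January 2024. At that date the procedural change could still protect the remaining 26 − 16 = 10, and the label can be put right for the whole trial before reporting.
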